## Discussion and conclusions

Our protocol aims to test the safety, feasibility and preliminary efficacy of a novel, neuromodulation therapy for intractable TPS. Our approach is based on the premise that failure of traditional cerebral neuromodulation in TPS with DBS [4,5,13,16] emerges from over-reliance on modifying the percept of pain by stimulating sensory-discriminative substrates that may be unviable owing to the offending lesions. Further, since the affective component of pain experience is equally, if not more important than the perceived intensity of pain, targeting regions such as VS/ALIC may successfully modify pain experience without necessarily modifying perception of pain intensity. The level of evidence, however, supporting efficacy for DBS in chronic neuropathic pain is mainly considered class III (descriptive case series, unblinded designs) [38], attributed to poor control of confounders of therapeutic benefit of neuromodulation. While addressing our research question, we have built study design refinements to potentially inform current and future clinical DBS trials in the field.

The ethical-scientific dilemma of introducing a control arm is particularly intense in neurosurgery, given the risk of interventions to the brain. However, since DBS allows for all patients to be implanted at first and then be randomized to active stimulation or sham, studies have explored randomized controlled designs in the use of DBS, particularly in movement disorders [39-42]. Thus, to balance ethical issues (potentially effective treatment compared against control or less effective treatment) with the importance of generating rigorous empirical evidence, we have incorporated a randomized, controlled, crossover design, where both active DBS and sham groups switch to the other intervention after 3 months from their initial randomization. That therapeutic benefits may carry over from the DBS into the sham phase cannot be completely discounted. By evaluating outcomes between active DBS and sham in the third month of corresponding treatments, we expect to minimize the influence of carry over; by noting difference in outcomes between the third month of the initial treatment and the first month of the intervention after crossover, we may also be able to define an adequate time lapse for future crossover studies.

Despite the inclusion of a placebo-controlled phase, altogether, patient expectations from undergoing a clinical-like investigational DBS procedure, therapeutic confusion within the investigative team, and unintentional cues during programming, can introduce several unwanted influences in clinical trial design. By introducing blinding for patients and employing a team where the investigator collecting outcome data is blinded and the surgeon and programming physicians are unaware of outcomes during the blinded phase, we aim to minimize unintentional cues and ensure investigator equipoise [22]. We are also minimizing unintentional cues by allowing adequate time (approximately 1 month) to elapse between programming for DBS and randomization to the intervention group, so that memory of the experience of stimulation is reduced. Nevertheless, a caveat exists. The therapeutic effects may influence patients’ perceptions, and thus, the integrity of experimental blinding [42]. For instance, early effects on mood and anxiety may inflate perceived benefits. To study this possibility, we will document the frequency with which patients can guess the allocated treatment and we will relate the Beck depression and anxiety inventories with PDI to note whether the placebo of DBS confounds therapeutic differences from the sham. We acknowledge, however, that small sample size may limit our ability to draw concrete inferences.

Finally, to allow systematic study of efficacy, adequate controls in enrollment and analysis would be critical. We are maintaining diagnostic consistency by restricting inclusion only to TPS etiology. Although such a step limits the sample size, it addresses the criticism of previous DBS studies where heterogeneity of etiologies and targets affected concrete conclusions about therapeutic efficacy [8]. With regards to analysis, instead of using the typical 50% response on the VAS as the success criterion, we base our choice of outcomes upon the intended therapeutic benefit. Because the affective experience of pain, rather than pain intensity itself, may be influenced with DBS of VS/ALIC, the Pain Disability Index has been chosen instead, and a success criterion with this measure has been defined at 40%. Since we anticipate a relation between affective and cognitive benefits and alleviation of pain disability, detailed neuropsychological pain, and cognitive and psychiatric assessments are explored to study interactions between pain, mood, anxiety, and depression, as well as personality and memory/experience, and the overall effect on quality of life. Long-term follow-up time points have been built into the design to allow calculation of long-term efficacy or stimulation tolerance. Last, our pilot study also represents the first attempt at investigating the proof-of-mechanism of a novel target of neuromodulation in TPS so that the influence of such targeting on pain networks can be described.

The benefits of DBS in chronic neuropathic pain, especially in TPS, are still less than adequate, to justify approval for widespread clinically labeled use. We propose that identifying better clinical alternatives in DBS may potentially improve efficacy of the approach. More importantly, however, it is incumbent on the field to incorporate well-controlled, blinded trial designs to explore the benefits of current as well as novel DBS targets. Based on recent recommendations, our trial involving DBS of the VS/ALIC may serve as an example of feasibly creating protocols that improve the quality of the evidence base.

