### Objectives and hypothesis

Here, we present the protocol design of our current pilot clinical trial where we examine: 1) safety and feasibility of delivering DBS to VS/ALIC in a double blinded, randomized, sham-controlled, crossover clinical trial in patients with TPS; 2) efficacy of the intervention with respect to pain-related disability, quality of life, neuropsychological and psychiatric outcomes and individual ratings of perception of pain; and 3) reorganization within affective networks of the pain neuromatrix with DBS delivered to VS/ALIC, which will be studied using functional magnetic resonance imaging (fMRI) and magneto-encephalography (MEG).

We hypothesize that DBS targeting VS/ALIC will modulate the affective component of TPS and consequently, improve pain-related disability.

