#### Phase IV: DBS programming and titration

DBS programming is initiated at least a month after DBS surgery to allow for resolution of microlesional effects. In acute programming, patients are asked to report changes in mood, anxiety, pain or suffering with activation of one or more electrode contacts. If the affective reporting of pain is not influenced, then settings affecting mood and anxiety can be chosen for chronic stimulation. All stimulation settings are planned below a charge density of 30 μC/cm^2^/phase, using the formula:

$$\begin{array}{c} \text{Charge}\;\text{density}\;\left({\mathrm{\mu C}/\mathrm{cm}}^{2}/\text{phase}\right)\\ =\frac{\text{Voltage}\;\left(V\right)*\text{Pulse}\;\text{width}\;\left(\mathrm{\mu s}\right)}{\text{Lead}\;\text{surface}\;\text{area}\;\left({\mathrm{cm}}^{2}\right)*\text{Impedance}\;\left(Ω\right)}\;\mathrm{Eq}.\;1 \end{array}$$

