### Feasibility of blinding

Our current trial is a double-blinded study where neither patients nor investigators performing outcome assessments know whether DBS or sham is delivered. Maintaining a blinded study is important because of the subjective nature of reports of pain and disability. Loss of blinding may occur due to the magnitude of the therapeutic effect or any other subjective perception that indicates that active DBS or sham is delivered. Safeguards have been incorporated to prevent loss of experimental blinding; for instance, stimulation is turned to 0 V after the programming and titration in phase IV to minimize the chance of memory of stimulation affecting the patient’s perception of receiving active DBS or sham in blinded phase V. In addition, patients and blinded investigators are asked separately via questionnaire, what they believe is the status of the stimulation (active or sham). At the end of the study, we will evaluate how effective the blinding strategy was in order to guide us forward.

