Both MEG and fMRI are exploratory in this study. With fMRI, one of our goals is to evaluate resting state fMRI, comparing networks when DBS is turned on versus when it is turned off. Patients will undergo resting-state fMRI at pre-operative baseline, during the randomized blinded phase and during follow up. Thus, by comparing the DBS-on and DBS-off conditions, we will be able to assess the effects of active versus sham DBS without confounds related to placebo or study-related effects. The next goal is to correlate changes in the neural networks related to the placebo effect; we intend to do so by comparing effects of DBS-off stimulation between active, sham and pre-operative baseline phases. With MEG, we aim to harness its high temporal resolution to assess possible effects of DBS on pain anticipation. The primary hypothesis is that DBS will have a significant effect upon the affective sphere of chronic pain. Pain anticipation is one of the conditions leading to pain habituation and chronic pain. Thus, we theorize that improvements in the affective sphere will also be correlated to how cortical networks in patients with TPS modulate in pain anticipation. In order to test this concept, we have created a visual paradigm of pain anticipation that consists of a simple, three-second countdown. The type of visual paradigm encodes whether or not a painful stimulus would follow the countdown. One of the limitations related to this paradigm is that we do not have a full characterization of how healthy individuals respond to pain anticipation in this task. This can limit our understanding of how processing of pain anticipation is abnormal in individuals with TPS, and could as well limit the interpretation of effects of active DBS. In order to address these limitations, we are also evaluating a cohort of 10 healthy subjects to allow comparisons.

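### The association between Beck scores and PDI cannot show placebo confounding, because the trial's own hypothesis predicts the same association

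*Protocol article*

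**What the plan says.** The Discussion and conclusions section of the protocol article is worried that "early effects on mood and anxiety may inflate perceived benefits". It names two checks. One is how often patients guess their allocation. The other is the Beck analysis: "we will relate the Beck depression and anxiety inventories with PDI to note whether the placebo of DBS confounds therapeutic differences from the sham". The paragraph closes with a caveat about small sample size and gives no other.

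Elsewhere the same relation is described as the intended effect:
- Objectives and hypothesis: "We hypothesize that DBS targeting VS/ALIC will modulate the affective component of TPS and consequently, improve pain-related disability".
- Secondary endpoints, in the imaging text: "The primary hypothesis is that DBS will have a significant effect upon the affective sphere of chronic pain".
- Phase IV (programming and titration): "If the affective reporting of pain is not influenced, then settings affecting mood and anxiety can be chosen for chronic stimulation". Mood change under active stimulation can thus be something the settings were selected to produce.
- Discussion and conclusions, in the paragraph after the Beck analysis: "Since we anticipate a relation between affective and cognitive benefits and alleviation of pain disability".

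On blinding, Feasibility of blinding adds that "patients and blinded investigators are asked separately via questionnaire, what they believe is the status of the stimulation", and accepts that blinding may be lost because the treatment works.

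**The concern.** One association carries two opposite meanings. In one paragraph of the Discussion it would indicate that placebo distorts the active-sham difference; in the next it is the expected therapeutic pathway. The article does not say how the two would be told apart.

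Under the stated hypothesis mood is a mediator. An association between mediator and outcome is what success looks like, so it cannot also serve as evidence of confounding.

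The trial offers itself as an example of better placebo control in DBS for pain and intends to inform the size of the placebo effect for phase II and III. Read as the placebo paragraph suggests, a real affective effect would count against itself. Read as the mechanism paragraph suggests, an expectation effect could pass as mechanism.

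**Working it through.** **Inputs from the article.** Enrolment is 10 patients, randomised 1:1, each receiving both conditions. The analysis is a paired t-test of the third month of DBS against the third month of sham, two-sided at 0.05. The earlier plan was 34 patients for an effect size of 0.5, equal to 7 PDI points, so the implied SD is 7 / 0.5 = 14. The article gives no figure for the Beck-PDI relation.

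**The plan's own figure.** A paired t-test with effect size 0.5, two-sided 0.05 and 80% power needs 33.4 patients, rounded up to 34 (power 80.8%). The stated 34 is reproduced. At n = 10 the power for the same effect is 29%. Below, 34 serves only as a larger sample for comparison.

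**Identifiability.** For each patient let M be the improvement in Beck score and P the improvement in PDI, active relative to sham.
- *True affective effect:* stimulation shifts M, and P = bM + e. Then corr(M, P) = b·SD(M) / √(b²·Var(M) + Var(e)).
- *Expectation or unblinding:* an expectation E moves both self-reports, M = λE + u and P = κE + v. Then corr(M, P) = λκ·Var(E) / √[(λ²·Var(E) + Var(u))·(κ²·Var(E) + Var(v))].

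Either expression can take any value between 0 and 1, so no observed correlation rules out either explanation. If expectation works wholly through mood, the second model has the same form as the first and the data are indistinguishable. Neither expression contains the mean difference between active and sham, so this correlation does not even depend on whether there is such a difference.

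Using the relation as an adjustment does not help. Under full mediation, the PDI difference adjusted for the Beck difference is zero although the treatment effect is real.

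**Illustration with assumed path sizes (SD units).**
- True affective effect: M has mean 0.7 and SD 1; P = 0.7M + e with SD(e) = 0.7. Population correlation: 0.7 / √(0.49 + 0.49) = 0.71.
- Expectation: E has mean 0.7 and SD 1; M = 0.85E + u with SD(u) = 0.53; P = 0.82E + v with SD(v) = 0.57. Population correlation: (0.85 × 0.82) / √[(0.7225 + 0.2809)(0.6724 + 0.3249)] = 0.697 / 1.000 = 0.70.
- No active-sham difference: as for expectation, but E has mean 0. Population correlation again 0.70.

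Results from 4,000 simulated trials per cell:

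| Scenario | n = 10: mean r (95% range) | n = 10: p < 0.05 | n = 34: mean r (95% range) |
|---|---|---|---|
| True affective effect | 0.69 (0.19 to 0.93) | 69% | 0.70 (0.50 to 0.85) |
| Expectation only | 0.68 (0.18 to 0.93) | 67% | 0.69 (0.48 to 0.84) |
| No difference | 0.68 (0.17 to 0.93) | 67% | 0.69 (0.47 to 0.84) |

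The larger sample narrows every range but does not separate the rows.

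**Precision, as a separate matter.** With n = 10, p < 0.05 requires |r| ≥ 2.306 / √(8 + 2.306²) = 0.63. For an observed r of 0.5, Fisher's z gives tanh(0.549 ± 1.96/√7), or -0.19 to 0.86. This is the limit the article admits; the identifiability problem would remain without it.

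**The companion check.** The article itself says that therapeutic effects may influence perception and so blinding. A correct guess can follow from real benefit, so guess frequency does not settle which reading applies.

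**Timing of the Beck scores.** The note to Table 1 puts the psychiatric examinations, which include both Beck inventories, at pre-operative baseline, randomization and months 12 and 24. The Phase II text says the assessments are repeated during the randomized phase. Any Beck-PDI analysis across active and sham needs scores from both blinded periods.

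**The case against.** The strongest reply is that this is one tentative sentence in a Discussion. It sets no threshold and no test, does not tell anyone to discount a PDI result, and carries a caveat. The statistical section does not list the analysis. The efficacy inference is the randomised paired comparison, and placebo is also approached through the crossover itself and the imaging comparison of stimulation-off states. The form of the analysis is open too: it could relate early mood to later PDI, or look within sham only, and a condensed article may leave that to a fuller document. Finally, the simulated correlations follow from chosen coefficients.

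Much of this stands and limits what may be said:
- A reader might infer that a true effect will be dismissed as placebo. With no decision rule fixed, the supportable statement is conditional: the explanations cannot be told apart, and a true effect would count as placebo only if the association is read as that sentence says.
- A reader might infer that the efficacy result is compromised. It is not; the third-month PDI comparison does not use this association.
- A reader might take 0.68 as an estimate for this trial. It is not; the near-equal values partly reflect the assumed paths. The argument rests on the two formulas.
- A reader might fault the article for not dating the treatment guesses. It places them in the blinded phase, and the exact visit may be in the full protocol.

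Two parts do not stand. The caveat concerns sample size, whereas the problem persists at any size. And the purpose of the analysis is stated, not omitted: as stated, it conflicts with the hypothesis. A within-sham analysis would avoid much of the difficulty, but the sentence refers to the active-sham difference and does not restrict itself to sham.

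**Conclusion.** The point holds in a limited form. Across active and sham, a Beck-PDI association is expected both under a true affective effect and under expectation or unblinding, so it cannot answer the question the Discussion sets for it, whatever the sample size. This follows from the article's own causal claim that affect changes first and disability follows. It does not depend on the simulated values, which are illustrative.

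What is affected is the conclusion the trial may draw about placebo confounding, which matters because placebo control is one of its stated contributions. The randomised PDI comparison is untouched. The text should be changed, at almost no cost.

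**What to change.** 1. In Discussion and conclusions, stop presenting the Beck-PDI association across active and sham as evidence of placebo confounding. Label it exploratory, as a description of mediation or mechanism, and state that it cannot distinguish a true affective effect from expectation.
2. Assess placebo from the PDI change from baseline under sham. Show patients who receive sham first separately (about 5 of 10 at 1:1), because they have no carry-over from a randomised active period. Examine any Beck-PDI relation meant to reflect placebo within that sham period only.
3. Report the planned treatment guesses by actual condition and period, with the reason for each guess, as description only. Do not treat the PDI difference by correct guess as a test: the guess comes after randomisation, true benefit can cause a correct one, and the subgroups would hold only a few patients.
4. Reconcile the note to Table 1 with the Phase II text so that it is clear whether Beck scores exist in both blinded periods.

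The cost is rewording, a little more descriptive analysis and, if not already asked, one questionnaire item for the reason behind the guess. The downside is a more modest claim about detecting placebo confounding. Change from baseline under sham also mixes expectation with the effect of surgery and natural variation, and with about 5 sham-first patients it will be imprecise.

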### Trial status

The trial is ongoing and is actively enrolling.

## Abbreviations

ALIC: anterior limb of internal capsule; BDI: Beck Depression Inventory; C-SSRS: Columbia-Suicide Severity Rating Scale; DBS: deep brain stimulation; DSMB: Data Safety and Monitoring Board; EuroQOL(EQ-5D): Euro Quality of Life scale; fMRI: functional magnetic resonance imaging; IPG: implantable pulse generator; MADRS: Montgomery-Asburg Depression Rating Scale; MCS: motor cortex stimulation; MEG: Magneto-encephalography; MRI: magnetic resonance imaging; NEO_FFI: NEO Five Factor Inventory; PANAS: Positive and Negative Affect Schedule; PDI: Pain Disability Index; TPS: thalamic pain syndrome; VAS: visual analog scale; VS: ventral striatum.
